#### KP phenotypes

We hypothesise that phenotypic markers representative of underlying pain mechanisms can be identified using self-report questionnaire items. Groups of questionnaire items will be entered into an exploratory structural equation model (ESEM) in order to identify underlying (latent) constructs (e.g. depression) being measured. ESEM also specifies the strength of association between each item and the underlying construct. Items showing the strongest association (*p* < 0.05) to each underlying construct will be shortlisted for inclusion within a developing tool which aims to classify underlying pain mechanisms in individuals reporting knee OA pain. ESEM will be conducted using M*Plus* 7.

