### Sample size

The sample size calculated was based on the primary objective of this study: to examine the natural history of KP within a community setting which involves the recruitment of as many knee pain positive and knee pain negative individuals with detailed exposure data captured from the questionnaire. The subsequent objectives are to examine the incidence, progression and associated risk factors.Source population: 40,000 questionnaires will be sent via post with a target of recruiting 10,000 participants (response rate 25%), which will form the source population of this study. Based on our previous studies, this would give 2500 people with knee pain (KP +) and 7500 people without knee pain (KP -). The sample size is 10 times larger than the subsequent sample size calculations for incidence, progression and risk factors of KP.Sample size for incidence and progression of KP: A sample of 730 participants will allow the detection of 3% (±1%) annual incidence of knee pain in a population over the age of 45^24^ at power of 90% (alpha 0.05, two-sided). This sample will also be able to detect a 14% occurrence of knee pain progression (worsening) (±5%) 24 at a power of 90% (alpha 0.05). An annual drop off rate of 30% plus 3% annual incidence rate of KP is excluded from the source population.Risk factors: A logistic regression model was used to calculate the sample size for one primary risk factor and multiple covariates. According to the annual incidence of 3% KP^24^ and an OR of 2 associated with overweight/obese [53] and assuming a multiple correlation coefficient of other covariates is 0.3, 702 participants are required for this risk factor analysis to give a power of 90% (alpha 0.05). For progression (i.e., 14% KP worsening), however, 203 participants are required.

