#### Reproducibility

For reproducibility of assessments, we will use the kappa-statistic for categorical data (x-rays and dichotomous US data) and the concordance correlation coefficient for continuous data. The magnitude of agreement on categorical data will be measured using the unweighted kappa statistic (for binary) or the weighted kappa statistics (for ordered categorical data) [56]. A numerical rating of kappa will be interpreted according to accepted criteria (0–0.2: slight; 0.2–0.4: fair; 0.4–0.6: moderate; 0.61–0.8: substantial; 0.81–1.0: almost perfect) and 95% confidence intervals will be reported [57]**.**

All analyses will be undertaken using Stata Statistical Software: Release 13 (StataCorp. 2013, College Station, TX: StataCorp LP). *P* values less than 0.05 will be considered significant.

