There are some limitations to the study design of KPIC. Firstly, being a questionnaire-based cohort study, the design is prone to a number of biases including response bias (participants with KP more likely to respond to the questionnaire) and recall bias (participants with KP may recall events and exposures more accurately compared to those without KP). However, the question on KP is very specific and focused on any symptoms in and around the knee for most days of at least one month in the previous 12 months which is the ‘gold standard’ for epidemiological research studies [30]. Current knee pain was defined as pain in or around the knees for most days of the past one month for incident knee pain. This was different from early onset knee pain which was defined as knee pain (ever or current for most days of at least a month) in the past 3 years. However, due to the transient nature of knee pain, it is possible that the baseline questionnaire might not allow us to correctly identify participants as being knee pain positive or knee pain negative (misclassification bias). A self-reported questionnaire approach also ensures the absence of interview bias from the study results [23]. Secondly, although the questionnaire cohort is large (*n* = 40,000), the clinical subset cohort is relatively small (*n* = 400). There may be limitations to using multiple adjusted effect estimates that have all been taken from a single logistic regression model. A bias otherwise known as the table 2 fallacy could occur where the interpretation of the confounder estimates may be different than for the exposure effect estimates [65]. Thirdly, there is a selection bias associated to a potential differential loss to follow-up in the group with moderate-severe pain or participants who are frail. The responders and non-responders will be compared at Year 1 and Year 3 in order to measure and subsequently adjust for this bias.

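### The p < 0.05 rule for shortlisting phenotype items tests whether a loading differs from zero, not whether it is strong

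*Protocol article*

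**What the plan says.** The section on KP phenotypes starts from the hypothesis that "phenotypic markers representative of underlying pain mechanisms can be identified using self-report questionnaire items". Groups of items go into an ESEM to find the latent constructs behind them. The article notes that "ESEM also specifies the strength of association between each item and the underlying construct", so the model supplies a measure of strength, namely the loading.

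The selection rule follows: "Items showing the strongest association (*p* < 0.05) to each underlying construct will be shortlisted for inclusion within a developing tool". The tool is one "which aims to classify underlying pain mechanisms in individuals reporting knee OA pain".

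No minimum loading, ranking, limit on cross-loadings or number of items per construct is given. No sample size is stated for this analysis. The Sample size section gives the targets for the questionnaire cohort: 40,000 mailed, 10,000 returned, 2,500 of these with knee pain and 7,500 without. The Discussion puts the clinical subset at 400.

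**The concern.** The rule speaks of the strongest associations but defines them by significance. A p-value depends on both the size of the loading and the number of people. In a sample of thousands, a loading far too small to be useful in a classification tool is significant.

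The second difficulty is specificity. ESEM estimates a loading for every item on every factor in the block. A tool meant to tell pain mechanisms apart needs items that belong mainly to one construct. Under a significance rule, an item with a large loading on one construct and a small one on another can qualify for both.

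What is at stake is the content of the shortlist, and so the tool-development aim. KP phenotypes feature in several of the listed objectives, and the Discussion presents them as a particular interest of the cohort.

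**Working it through.** **Inputs**
- Rule: p < 0.05 on the loading, taken as two-sided because sidedness is not stated there.
- Questionnaire cohort: 40,000 × 0.25 = 10,000 responders, which reproduces the article's target. The 2,500 with knee pain is 25% of these, which agrees with the article's own split.
- ESEM sample: not stated. The items are questionnaire items and the tool is for people reporting knee OA pain, so I assume n between 2,500 and 10,000. I use n = 400 (the clinical subset) as a lower check.

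**Step 1: smallest significant loading, treating a loading as a simple correlation**

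Threshold = tanh(1.96/√(n − 3)).
- n = 2,500: 1.96/√2,497 = 0.039; squared, 0.0015 (0.15% shared variance).
- n = 10,000: 1.96/√9,997 = 0.020; squared, 0.0004 (0.04%).
- n = 400: 1.96/√397 = 0.098; squared, 0.0096 (about 1%).

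**Step 2: probability that a weak item passes, same approximation**

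Probability = Φ(atanh(λ)·√(n − 3) − 1.96), where λ is the true loading.
- λ = 0.10, n = 2,500: 0.1003 × 49.97 − 1.96 = 3.05, giving 0.999.
- λ = 0.05, n = 2,500: 0.0500 × 49.97 − 1.96 = 0.54, giving 0.71.
- λ = 0.05, n = 10,000: 0.999.
- λ = 0.20, n = 400: 0.98.

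**Step 3: check against rotated loadings**

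Rotated loadings have larger standard errors than simple correlations, so Step 1 is optimistic about precision. A simulation was run with a two-factor maximum-likelihood model and oblimin rotation. Its assumptions: 14 continuous items, 12 with main loading 0.6, one with 0.1, one with 0.2, factor correlation 0.3, 150 replicates. The standard errors below are for the 0.1 item.

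| n | SE | Threshold (1.96 × SE) | Loading 0.1 passes | Loading 0.2 passes | Loading 0.6 passes |
|---|---|---|---|---|---|
| 400 | 0.0623 | 0.122 | 0.34 | 0.93 | 1.00 |
| 2,500 | 0.0251 | 0.049 | 0.95 | 1.00 | 1.00 |
| 10,000 | 0.0123 | 0.024 | 1.00 | 1.00 | 1.00 |

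The simulation error on the 0.95 is about √(0.95 × 0.05/150) = 0.018. For λ = 0.05 at n = 2,500, the same standard error gives Φ(0.05/0.0251 − 1.96) = Φ(0.03) = 0.51, against 0.71 in Step 2.

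At n = 2,500 and above, items loading 0.2 (0.2² = 4% shared variance) and 0.6 (0.6² = 36%) both passed every time. The rule treats them alike.

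**Step 4: cross-loadings**

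In the same simulation, the standard error of a strong item's loading on the other factor was 0.0172 at n = 2,500 and 0.0088 at n = 10,000. A cross-loading of 1.96 × 0.0172 = 0.034, or 1.96 × 0.0088 = 0.017, is then significant, and the item meets the stated rule for both constructs.

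**Step 5: a smaller sample**

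Some psychosocial items enter only at Year 1 (Table 1; Year 1 follow-up). With the article's 30% annual drop-off, 2,500 × 0.70 = 1,750. The Step 1 threshold becomes 0.047, and a loading of 0.10 passes with probability 0.987.

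**The case against.** The strongest reply is that the word *strongest* already implies selection by size, with p < 0.05 only as a floor, and that loading cut-offs are normally left to an analysis plan. The items are also only shortlisted for a tool still in development. The Abbreviations list the Comparative Fit Index and the Tucker Lewis Index, which the analysis text never uses, so some planned model assessment may have been condensed away.

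Part of this stands. A ranking may be intended, and an unstated cut-off alone would be no finding. But the article does state a numerical criterion, attaches it directly to *strongest*, and gives no other. Global fit indices judge the model as a whole and would not supply an item-selection rule.

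Three stronger readings are tempting, and the document does not support them:
- *That almost any item would pass.* An item with a true loading of zero fails about 95% of the time. Items grouped because they are thought to measure a construct will seldom sit at zero, but the true loadings are unknown.
- *That the finished tool could not separate mechanisms.* This depends on unknown loadings and cross-loadings, and rotation is meant to keep cross-loadings small. What can be said is that the rule does nothing to ensure separation.
- *That selection and performance would be judged on the same data.* The article describes no performance assessment of the tool, and the questionnaire is repeated at Years 1 and 3, so nothing can be concluded either way.

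It is also fair to object that 2,500 is a recruitment target and not a stated ESEM sample, and that the simple-correlation formula understates the standard error. The ranges above allow for both.

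**Conclusion.** The concern holds as a fault in the stated criterion: p < 0.05 measures detectability, and the article uses it to define strength. Taking both methods together, the smallest loading that passes is about 0.04 to 0.05 at n = 2,500 and 0.020 to 0.024 at n = 10,000. A true loading of 0.10 passes with probability about 0.95 to 0.999 at n = 2,500. At n = 400 the threshold rises to about 0.10 to 0.12, and a loading of 0.20 still passes with probability 0.93 to 0.98, so the conclusion largely survives there.

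This rests on the assumed ESEM sample, a two-sided test and, for the simulated figures, the assumed factor model with continuous items. Ordinal items with other estimators would have somewhat larger standard errors, which would not change the direction. The consequence is confined to the phenotype tool.

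**What to change.** Before the ESEM is run, state what *strongest* means in terms of effect size. Either of these would do:
- a pre-specified minimum standardised loading on the target construct and a maximum loading on every other construct, for example at least 0.40 and below 0.30; or
- a fixed number of items per construct, ranked by standardised loading.

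The figures 0.40 and 0.30 are illustrative and do not come from the article. What matters is that the limits are set in advance, so that they are not chosen after the loadings are seen. Keep p < 0.05 at most as a secondary condition, and state which responders and which questionnaire wave the ESEM uses.

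Confirming the loadings in a random half of the sample or in a later wave is an optional addition. A split of 2,500 would leave 1,250 for derivation.

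The cost is small: a change to the analysis text and a shorter item list. No new data are needed.

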#### Reproducibility

For reproducibility of assessments, we will use the kappa-statistic for categorical data (x-rays and dichotomous US data) and the concordance correlation coefficient for continuous data. The magnitude of agreement on categorical data will be measured using the unweighted kappa statistic (for binary) or the weighted kappa statistics (for ordered categorical data) [56]. A numerical rating of kappa will be interpreted according to accepted criteria (0–0.2: slight; 0.2–0.4: fair; 0.4–0.6: moderate; 0.61–0.8: substantial; 0.81–1.0: almost perfect) and 95% confidence intervals will be reported [57]**.**

All analyses will be undertaken using Stata Statistical Software: Release 13 (StataCorp. 2013, College Station, TX: StataCorp LP). *P* values less than 0.05 will be considered significant.

## Discussion

A population-based prospective cohort study is needed to determine the natural history of KP, involving affected and unaffected people at baseline, to examine the incidence, progression, different KP phenotypes and associated risk factors and outcomes. Results from our study can provide an insight into possible pain phenotypes according to self-reported factors such as intermittent versus persistent KP, localised versus generalised KP, qualitative descriptors of KP that suggest central sensitisation, and presence of multiple regional pain.

The advantages of KPIC in comparison with other studies published so far include the focus on the entire spectrum of knee pain, the long follow-up duration (three years in the first instance), the repeated measures of both exposures and outcomes at several time points and the battery of clinical assessments in people with early KP, no KP and established KP. It is important that the KPIC study population is representative of the general population (See Additional file 3). The inclusion criteria is set slightly younger (40 years and above) than other population cohorts such as the Genetics of OA and Lifestyle study (45 years and over) and the British National Survey (55 years and over) in order to capture more participants with any symptoms or radiographic signs of early OA as opposed to established KP which has already been extensively researched but mainly in people over 50 [58–62].

The expected response rate of 25% is lower than the mean response rate of 60% for postal surveys published in medical journals [63]. However, this is based on previous surveys to the community in Nottingham and this rate could be improved with the use of reminder letters and an accompanying postal questionnaire. The response rate could also be improved with the use of financial incentives, however, there is limited evidence to support this [64]. In order to retain participants through the course of the KPIC timeline, the authors will ensure timeline questionnaire reminders (4–6 weeks) post initial questionnaire mail out as well as annual newsletters with updates on study progression such as successful recruitment to a sub-study and preliminary findings.

There are some limitations to the study design of KPIC. Firstly, being a questionnaire-based cohort study, the design is prone to a number of biases including response bias (participants with KP more likely to respond to the questionnaire) and recall bias (participants with KP may recall events and exposures more accurately compared to those without KP). However, the question on KP is very specific and focused on any symptoms in and around the knee for most days of at least one month in the previous 12 months which is the ‘gold standard’ for epidemiological research studies [30]. Current knee pain was defined as pain in or around the knees for most days of the past one month for incident knee pain. This was different from early onset knee pain which was defined as knee pain (ever or current for most days of at least a month) in the past 3 years. However, due to the transient nature of knee pain, it is possible that the baseline questionnaire might not allow us to correctly identify participants as being knee pain positive or knee pain negative (misclassification bias). A self-reported questionnaire approach also ensures the absence of interview bias from the study results [23]. Secondly, although the questionnaire cohort is large (*n* = 40,000), the clinical subset cohort is relatively small (*n* = 400). There may be limitations to using multiple adjusted effect estimates that have all been taken from a single logistic regression model. A bias otherwise known as the table 2 fallacy could occur where the interpretation of the confounder estimates may be different than for the exposure effect estimates [65]. Thirdly, there is a selection bias associated to a potential differential loss to follow-up in the group with moderate-severe pain or participants who are frail. The responders and non-responders will be compared at Year 1 and Year 3 in order to measure and subsequently adjust for this bias.

Knowledge obtained from this proposed cohort study could be important for understanding the natural history of KP, including incidence, in a community-based population setting. Currently, we are unaware of any other population-based cohort established for people at risk for KP, therefore this is the first cohort to cover the full natural history from no KP to KP, then to the outcomes of KP. In addition, we are not only interested in KP severity but also KP phenotypes. Identifying specific subgroups or phenotypes of people with KP and possible novel associations with each phenotype are important as it may help to develop specific individualised treatment or management strategies. The cohort will also help us to understand the implications of central sensitisation versus localised pain features and use this to improve the diagnosis, treatment and management of KP and knee OA in the general population.

## Abbreviations

2D4D: 2ND digit and 4th digit ratio
ANOVA: Analysis of Variance
AS: [name]
AV: [name]
CCC: Concordance Correlation Coefficient
CFI: Comparative Fit Index
CI: Confidence Interval
CM: Centimetre
CPM: Central Pain Modulation
CRP: C reactive protein
CTX-II: C-telopeptide of type II collagen
DNIC: Descending noxious inhibitory control
DW: [name]
EPIC: European Prospective Investigation into Cancer study
ESEM: Exploratory Structural Equation Model
GOAL: Genetics of Osteoarthritis and Lifestyle study
GP: General Physician
GPPAQ: General Practice Physical Activity Questionnaire
GSF: [name]
HADS: Hospital Anxiety and Depression Scale
HDHA: Hydroxy-docosahexaenoic acid
HFCS: High Fructose Corn Syrup Study
HSE: Health Survey of England study
ICOAP: Intermittent and Constant Osteoarthritis Pain
IL: Interleukin
KA: [name]
KL: Kellgren Lawrence
KP: Knee Pain
KPIC: Knee Pain in the Community
LM: [name]
LOT: Life Orientation Test
MD: [name]
mN: Millinewton
NF: [name]
NLDA: Nottingham Line Drawing Atlas
NREC: Nottingham Research Ethics Committee
NRS: Numerical rating scale
OA: Osteoarthritis
OR: Odds Ratio
PA: Posterior-anterior
PCS: Pain Catastrophising Scale
PDQ: Pain Detect Questionnaire
PF: Patellofemoral
PPT: Pain Pressure Thresholds
QST: Quantitative Sensory Testing
ReR: Response Rate
TF: Tibiofemoral
TNF: Tumor Necrosis Factor
TS: Temporal summation
Tucker Lewis Index: Tucker Lewis Index
WZ: [name]
